## Methods

### Study Design and Setting

This is a 2-armed, single-blinded, randomized controlled trial (RCT) that will be conducted among Malaysian youths with ACEs at the Department of Clinical and Health Psychology, National University of Malaysia. Briefly, the intervention group includes an evidence-based curriculum and components such as emotion regulation, active coping and goal setting, cognitive flexibility, mindfulness-based stress reduction, social support, self-exploration, resources and navigation, and finally, spirituality and religion. Participants in the control group will not receive any form of intervention. The main outcome of this study is resilience among youths with ACE while the secondary outcomes include coping, psychological well-being, quality of life, subjective stress, perceived stress, personal resources, and adult resilience. These variables will be evaluated at baseline and postintervention. Intention-to-treat analysis will also be performed. This clinical trial has been registered with the Australia New Zealand Clinical Trials Registry (trial Id: ACTRN12622000604707).

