**Assessments**										
	Brief Coping Orientation to Problem Experienced Scale - English and Malay version	✓				✓		✓		
	Ryff’s Scale of Psychological Well-being (SPWB) - English and Malay version	✓				✓		✓		
	Quality of Life –WHOQL-BREF - English and Malay Version	✓				✓		✓		
	Subjective stress – Perceived Stress scale - English & Malay version	✓				✓		✓		
	Personal Resources Questionnaire 2000 - English and Malay version	✓				✓		✓		
	Adult Resilience Measure-Revised - English and Malay version	✓				✓		✓		
	Biomarker - measure changes in salivary cortisol	✓				✓				
	Blood pressure (blood pressure measured with a sphygmomanometer	✓				✓				

Participants in the control group will receive no intervention, while those in the intervention group will receive five sessions of resilience-building intervention conducted by a trained facilitator. Hotlines, post session, and appropriate resources will be provided for those reporting distress after the intervention. Investigators will be blinded throughout the whole process of randomization and data collection as the whole process is handled by a research assistant (randomization), counsellor, and clinical psychologist (data collection). Under no circumstances will unbundling occur as a research assistant, counsellor, and clinical psychologist are briefed with the standard operating procedure to follow when an incident occurs. The flow diagram is presented in Figure 1.

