#### Time Points for the Primary Outcomes and Retention

Premeasurements will be conducted at baseline, whereas postmeasurements will be collected after the fifth session as shown in Figure 1. Participants will be given Ringgit Malaysia 50 after the third and fifth sessions of the intervention to ensure they do not drop out of the study. Another follow-up will be conducted 4 weeks after the Intervention.

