### Data Analysis

All data management and statistical analysis will be conducted using SPSS (version 26; IBM Corp). Data management will be performed by screening for missing data and checking for potential outliers. Descriptive statistics will be used to assess the data normality and to summarize the pre and postintervention scores for each group at different periods. Mean and SDs will be provided for normally distributed data, followed by mixed ANOVA with repeated measures to compare the pre and postintervention mean scores between and within the groups.

The assumptions of ANOVA include randomly collected and normally distributed data, sufficient sample size, homogeneity of variances, and absence of violation and outliers. Levene’s test will be applied to test the homogeneity of variance. Mixed ANOVA benefits RCT design as it allows testing for 2 groups across 2-time points. Mixed ANOVA analysis aims to handle response outcomes conducted on the same experimental unit at a different time or under different conditions [57]. The differential effects of the intervention components will be tested with interactions between the component and time. These analyses will model random slopes and intercepts for participants, explore the fixed effects of the condition, and test the repeated measures over time. This type of analysis is advantageous by accounting for missing values through the maximum likelihood estimation method [57]. Effect sizes will be computed based on Cohen *d*.

In addition, the intention-to-treat analysis will be applied to analyze the participants according to their assigned groups. This analysis includes all participants and ignores noncompliance, protocol deviation, and withdrawal. The intention-to-treat analysis is a complete trial strategy for the design, execution, and analysis of RCT, focusing on the consolidated standard of reporting trial guidelines. Thus, the number of participants in each assigned group will be analyzed by the intention-to-treat principle.

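### Component-by-time effects cannot be separated from arm-by-time, because one arm gets the whole package and the other nothing; the random-slope wording also does not fit the two-visit analysis described

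*Protocol article*

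**What the plan says.** All references are to the protocol article.

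- **Component test.** Data Analysis states: "The differential effects of the intervention components will be tested with interactions between the component and time".
- **Model.** The next sentence reads: "These analyses will model random slopes and intercepts for participants, explore the fixed effects of the condition, and test the repeated measures over time".
- **Time points in the analysis.** The same section plans to "compare the pre and postintervention mean scores between and within the groups" and adds: "Mixed ANOVA benefits RCT design as it allows testing for 2 groups across 2-time points". Study Design and Setting agrees: "These variables will be evaluated at baseline and postintervention".
- **Time points in the schedule.** Time Points for the Primary Outcomes and Retention places the post measurement after the fifth session and adds: "Another follow-up will be conducted 4 weeks after the Intervention". The Abstract also mentions this visit. Table 1 ticks it for the six questionnaires, including the adult resilience measure, but not for salivary cortisol or blood pressure.
- **Exposure.** The text after Table 1 says that controls receive nothing, while "those in the intervention group will receive five sessions of resilience-building intervention". Contents and Delivery Method of the Intervention says that all sessions go to each participant, one per week from week 1 to week 5.

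**The concern.** To estimate a component's own effect, some participants must receive it while otherwise comparable participants do not, or outcomes must be measured before and after it is delivered. This trial has neither feature. It compares a complete package with nothing, and outcomes are taken only before the first session and after the last. A claim about which component works would have no basis in the randomised comparison.

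The random-effects wording raises a separate and smaller question. A random intercept and a random slope with residual error ask for more covariance parameters than two measurements per person can supply. The analysis text and the assessment schedule disagree on whether there are two visits or three.

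Timing matters because the Results section reports that preliminary analysis is under way and that final analysis is due by March 2025. An analysis found to be impossible at that stage would have to be replaced after results had been seen.

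**Working it through.** **Plan's own figure.** None is attached to the component test. The only sizing figure, N = 36, is for the two-group within-between interaction at f = 0.25, α = 0.05 and power 0.80. The article gives neither the number of measurements m nor their correlation ρ. With noncentrality λ = f²·N·m/(1−ρ), and assuming m = 2 and ρ = 0.5, the required N is 34 (power 0.807); N = 36 gives power 0.830. At m = 2 the required N runs from 66 (ρ = 0) to 22 (ρ = 0.7). The stated figure is thus plausible for arm-by-time, and no component test was sized.

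**Step 1: component terms.** Let G be 1 for the intervention arm and 0 for control. Let C₁ to C₈ be indicators for the eight components in Study Design and Setting. Everyone with G = 1 is assigned all components and everyone with G = 0 none, so C₁ = … = C₈ = G. Each Cⱼ × time column then equals G × time. For 25 + 25 participants:

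| Visits | Columns (intercept + time + components + interactions) | Rank | Interaction columns | Rank of interaction block |
|---|---|---|---|---|
| 2 | 1 + 1 + 8 + 8 = 18 | 4 | 8 | 1 |
| 3 | 1 + 2 + 8 + 16 = 27 | 6 | 16 | 2 |

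The interaction rank (1 or 2) is exactly that of arm-by-time alone. A third visit, a larger sample or a different component list changes nothing, because all the indicators remain the same column.

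**Step 2: random intercept and slope at two visits.** Code time as 0 and 1. Let a be the intercept variance, b the intercept-slope covariance, c the slope variance and s the residual variance.

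- Var(Y₀) = a + s
- Cov(Y₀, Y₁) = a + b
- Var(Y₁) = a + 2b + c + s

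These are three equations for four parameters (Jacobian rank 3). Changing (a, b, c, s) by (−δ, +δ, −2δ, +δ) leaves all three unchanged; for the last, −δ + 2δ − 2δ + δ = 0.

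**Step 3: does this reach the treatment effect?** With complete data, the standard error of group-by-time is √[(c + 2s)(1/n₁ + 1/n₂)]. Under the same shift, c + 2s becomes c − 2δ + 2s + 2δ, which is unchanged. As an illustration with assumed variances of 1 and correlation 0.5:

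- s = 0 gives a = 1, b = −0.5, c = 1, so c + 2s = 1.
- s = 0.25 gives a = 0.75, b = −0.25, c = 0.5, so c + 2s = 1.

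With 25 per arm, both give a standard error of √(1 × 2/25) = 0.283. With missing values the likelihood still depends only on the marginal 2 × 2 covariance, which is identified, so the conclusion stands.

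**Step 4: three visits.** At times 0, t₁ and t₂ there are 6 covariance elements for the same 4 parameters. Cov(0, t₁) = a + b·t₁ and Cov(0, t₂) = a + b·t₂ give a and b. Cov(t₁, t₂) = a + b(t₁ + t₂) + c·t₁·t₂ gives c, and Var(Y₀) then gives s. The rank is 4 and the model is identified, for example with visits at 0, 5 and 9 weeks.

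**The case against.** **Component may be a slip for condition.** The following sentence speaks of the fixed effects of the condition. No component hypothesis appears in the Objective, the outcome list or the sample size. On that reading the sentence describes the ordinary group-by-time test, which is estimable. This is plausible and lowers the stakes, but the sentence as printed is still wrong and needs rewording.

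**The random-slope model might seem to make the trial's standard errors arbitrary or prevent a fit.** A reader might infer this from the parameter count, but it does not follow. Only the division of variance between the random effects and the residual is undetermined (Step 3). Software may warn about convergence or the Hessian.

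**The trial might seem to have only two time points.** That too is a tempting inference from the analysis text, but the schedule gives all six questionnaires a third visit. A linear random slope is identified there and is an acceptable choice. Only cortisol and blood pressure are always two-visit outcomes, and neither is in the main and secondary outcome list of Study Design and Setting.

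**Attendance might seem a likely substitute for component exposure.** Attendance could vary within the intervention arm, but a comparison based on it would be non-randomised. The article plans no such analysis, and its intention-to-treat rule sets noncompliance aside. It would be conjecture to say that the investigators intend one.

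**Conclusion.** The component-by-time analysis, as written, cannot be carried out: the terms are completely aliased with arm-by-time at two visits and at three. This rests only on the stated design, in which all sessions go to one arm in one order, none go to the other, and no outcome is measured between sessions.

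The random-slope issue is secondary. The two-visit analysis text conflicts with a schedule that gives the questionnaires three visits. At two visits the variance components are not separately identified (4 parameters, rank 3); at three they are (rank 4). The treatment inference is sound in both cases.

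This should be corrected before the final analysis, but it does not undermine the trial. The between-group comparison is planned separately in the same section and remains estimable, and the defect lies in the wording of the analysis.

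**What to change.** 1. Delete the component-by-time sentence. If *component* was meant as *condition*, replace it with the group-by-time interaction.
2. State that the trial estimates the effect of the whole package only, and that any summary by session attendance is descriptive.
3. State that the questionnaire model uses all three scheduled visits, and bring the two-time-point wording in Data Analysis and in Study Design and Setting into line with Table 1.
4. For outcomes measured twice (cortisol and blood pressure), drop the random slope. An unstructured within-person covariance gives the same treatment inference and keeps the planned maximum-likelihood handling of missing values.

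The cost is a few lines of text. Data collection and sample size do not change. The investigators give up a claim about individual components that this design could not have supported.

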#### Criteria for Discontinuing or Modifying Intervention

All the intervention modules were well understood by the participants enrolled in the pilot test; hence, no attempt has been made to review the intervention. Participants have the right to withdraw from the research at any given time if they do not feel comfortable continuing with the study. If the counselor or clinical psychologist reviews and discusses the harm of the participants continuing to participate in the research project, they will advise the participants to drop out of the study based on their professional judgment. A panel comprising counselors, and clinical psychologists will jointly review the case and make a consensus decision.

#### Data Auditing and Management

The team is required to submit first and second progressive reports to the Research Ethics committee, at the National University of Malaysia as part of the auditing process. Only group data will be reported. Data will be reported collectively; individual data will not be disclosed. Journal and progress of group sessions will be collected from mental health professionals after each session to ensure they continue a similar structure for the intervention. The checklist will be prepared for the mental health professionals.

As for data storage and management, the data will be entered digitally and stored in a Microsoft Excel sheet and Microsoft Word document by the investigator after being collected from mental health professionals. Each dataset will be assigned a code to protect the participants’ identity. The encryption of the firewall will help secure and protect the data. A passcode will be generated to protect these documents. The data will be stored in the institution for 5 years, kept confidential and used only for educational purposes.

#### Standard Operating Procedure to Manage Harm

Counsellors and clinical psychologists will evaluate if any of the participants feel discomfort or express interest in withdrawing from the studies. This assessment will be carried out during the break intervals between each session of the intervention and the follow-up periods post intervention. Participants will be asked verbally if they still feel comfortable and willing to proceed with the intervention. Follow-up and proper redirecting to resources will be practiced with individuals who dropped out of the study.

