This intervention aims to focus on vital resilience components which are emotion regulation, active coping and goal setting, cognitive flexibility, physical health, mindfulness-based stress reduction, social support, self-exploration, resources and navigation, financial planning, and spirituality and religion. One of the weaknesses of this intervention is that these components will be monitored by informal assessment such as observation, tracking, and recap to ensure participants have learned and acquired the tools and knowledge. It is also difficult to ensure participants from the control group will not receive any form of therapy during the whole duration of the intervention. Hence, the therapist has to check in with the group from time to time to ensure their well-being is taken care of. If needed, the therapist will conduct a post-group counselling session with an individual who is distressed by the intervention. Given that the participants were selected from a pool of individuals obtaining a specific level of ACEs, the findings might not be generalized to the entire population of people with ACEs in the country.

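### The harm check is promised for every participant but timed and worded for the intervention arm, so controls have no scheduled check in weeks 1 to 5

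*Protocol article*

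**What the plan says.** All references are to the protocol article.

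- **Standard Operating Procedure to Manage Harm.** Counsellors and clinical psychologists are to look for discomfort, or a wish to withdraw, in any participant; no arm is named. The timing is then fixed: "This assessment will be carried out during the break intervals between each session of the intervention and the follow-up periods post intervention". So is the question: "Participants will be asked verbally if they still feel comfortable and willing to proceed with the intervention". For leavers, "Follow-up and proper redirecting to resources will be practiced with individuals who dropped out of the study".
- **Text after Table 1.** "Participants in the control group will receive no intervention". On support, hotlines are mentioned and "appropriate resources will be provided for those reporting distress after the intervention".
- **Discussion, Principal Findings.** The authors note that it is "difficult to ensure participants from the control group will not receive any form of therapy during the whole duration of the intervention". The next sentence says that "the therapist has to check in with the group from time to time to ensure their well-being is taken care of". The one after it offers counselling: "the therapist will conduct a post-group counselling session with an individual who is distressed by the intervention".
- **Criteria for Discontinuing or Modifying Intervention.** Any participant may withdraw. A panel may review harm, and the stated action is advice to leave the study.
- **Contents and Delivery Method, with Table 2.** Sessions are weekly in weeks 1 to 5. Each is described as two 60-minute parts with a 15-minute break, but Table 2 shows the fifth as one 120-minute block.

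**The concern.** The procedure promises cover for everyone and then sets a time and a question that only someone attending sessions can meet. Both arms are selected for an ACE score of four or more, so a control can become distressed too. Entry also excludes people receiving any intervention, so controls start without current care.

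Two things are at stake, both modest. The first is protection: during weeks 1 to 5 nothing clearly stated gives a distressed control who stays in the study a scheduled check or a route to support. The second is reporting: sessions 3B and 4A go back over past adversity, so readers will want to know whether the sessions upset people. Harms noted only at session breaks come from one arm and could be misread as comparative when the trial is reported.

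**Working it through.** The article states no number of harm checks, so there is no figure to reproduce. The check is a side-by-side reading, a count, and the precision of the proposed remedy.

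**1. What reaches a control in weeks 1 to 5**

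| Provision | Reaches a control who stays in the study, weeks 1 to 5? |
|---|---|
| Session-break check | No: controls have no sessions |
| Follow-up check | May cover both arms, but falls after the intervention, and the question does not fit controls |
| Therapist's check-in (Discussion) | Probably: it directly follows a sentence on controls; no schedule |
| Hotlines and resources | Unclear: the wording may mark only a time point, but that point is after the intervention |
| Post-group counselling | No: it is for distress caused by the intervention |
| Redirecting to resources | May cover both arms, but only after dropping out |
| Right to withdraw, panel review | May cover both arms; the stated action is advice to leave |

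**2. Scheduled checks per participant, weeks 1 to 5**

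- Intervention arm: sessions 1 to 4 have one break each, giving 4. Session 5 adds 1 only if its 120-minute block has a break, giving 5. Counting instead the gaps between five weekly sessions gives 5 − 1 = 4. The range is 4 to 5.
- Control arm: 0.
- With 25 per arm and full attendance: 25 × 4 = 100 to 25 × 5 = 125 checks, against 0.

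**3. What the proposed question could show**

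The 95% half-width for a difference between two proportions, with the same proportion p reporting distress in each arm and n per arm, is 1.96 × √(2p(1 − p)/n). The values of p are assumptions; the article gives none.

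| p | n = 25 | n = 11 |
|---|---|---|
| 0.10 | 0.166 | 0.251 |
| 0.20 | 0.222 | 0.334 |
| 0.30 | 0.254 | 0.383 |

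For example, 1.96 × √(2 × 0.10 × 0.90/25) = 0.166. The case n = 11 supposes that only those not yet recruited can be asked: 50 − 28 = 22, split equally. With half-widths of 17 to 25 percentage points at best, the question gives a descriptive safety record and no test.

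**4. Answers that may be missing**

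The Results section reports 28 recruited. If all of them are past the follow-up contacts, 28/50 = 56% of the planned sample cannot be asked. The share is larger if recruitment closes below 50.

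**The case against.** The strongest reply has four parts.

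*An article condenses a fuller protocol.* A support list for controls may well sit in the full operating procedure or the information sheet. That stands for the missing schedule of the check-in and for who is meant by the group; those alone would be missing detail and no finding. It does not cover the harm check, because there the article states the rule, and the rule's time and question do not match its stated scope.

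*Monitoring follows exposure.* Only the intervention arm discusses past adversity, so checking tolerability at the sessions is sensible. This stands, and the checks should stay.

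*Controls are at lower risk than the ACE score suggests.* Severe psychopathology, and psychiatric illness needing medication, are excluded. This also stands and is one reason for the low severity.

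*Little can still be changed.* Recruitment was due to close on 30 January 2025 and final analysis by March 2025. This limits the data that the fix can yield, but not the wording on support or the need to label one-arm data as such.

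A reader might go further and infer that controls are left with no monitoring or support at all. The article does not support that: the check-in probably reaches them, and withdrawal, panel review, follow-up checks and redirection of leavers may cover both arms. A reader might also infer a failed safety comparison; the article never claims to make one. Nor is it right that Table 1 offers nothing comparable by arm: the questionnaires, cortisol and blood pressure are measured without distinction of arm, though none is a dedicated harm item.

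**Conclusion.** The point holds at low severity. As written, the harm check gives 4 to 5 scheduled occasions per intervention participant in weeks 1 to 5 and none per control, and the stated support is worded around the intervention. The consequence is a small gap in participant protection and a risk that one-arm harm observations are read as comparative. The primary estimate is unaffected.

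The count assumes that a break interval means the pause inside a weekly session, or else the gap between sessions. Adding both kinds together would give 8 to 9, but a week-long gap is hardly a break, and that count should not be used. Nor should the 28 days from the first to the fifth session (4 × 7) be taken as the time a control goes without scheduled contact. The relevant interval runs from allocation to the post-intervention assessment, and the article does not state it.

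**What to change.** 1. Keep the session-break checks, and report them as tolerability data from the intervention arm only.
2. At the follow-up checks already provided for (post-intervention and four weeks later), replace the question on proceeding with the intervention by one identical, arm-neutral question on distress or adverse events since the last assessment. Ask it in both arms. Participants complete it themselves, on paper or online, after the outcome measures. Report it descriptively by arm, with the number not asked.
3. Reword the text after Table 1 and the Discussion so that hotlines, resources and counselling are open to any distressed participant in either arm. Give both arms the contact list at allocation.
4. If no one is left to ask, state in the report that no comparable control harm data exist.

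The cost is one question at two existing contacts, a contact list and some rewording, with no extra staff. There are three downsides. Controls who seek help slightly dilute the contrast. An answer that mentions a session could reveal the arm to a blinded assessor, which is why self-completion comes after the outcome measures. Answers will be missing for those already past the contacts, up to 28 of the planned 50.
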